Our specific hypotheses include that: (1) early (<2 hours) USPIO-enhanced imaging will principally reflect vascular distribution and will correspond with other MRI-derived measures of tumor vascular density and perfusion; (2) delayed (24–48 hours) USPIO-enhanced imaging will principally reflect intracellular USPIO distribution within TAM, and will co-localize with but also extend beyond imaging (GBCA enhancement) and tissue markers of endothelial disruption; (3) that QSM-derived susceptibility estimates and T2*-based measures will provide optimal quantitative reliable measures of TAM density, iron abundance and cellular iron localization with imaged tumors; (4) susceptibility based measures of delayed USPIO uptake (e.g., QSM, R2* mapping) will be greater in growing VS, relative to non-growing tumors, and will reflect an increased abundance of TAM in these tumors; and (5) that regions of higher grade transformation within imaged glioma will show changes on delayed USPIO-enhanced acquisitions, in particular susceptibility-based measures such as QSM, and these regions will show greater TAM abundance on matched tissue sections compared to non-enhancing tumor regions.

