### Tissue collection

2.4.

Written informed consent is obtained from all participants for the collection and analysis of tumor tissue, with both formalin-fixed paraffin-embedded (FFPE) and fresh-frozen specimens collected at surgery. Immunohistochemistry and immunofluorescence analyses are performed on FFPE and fresh-frozen tissue to characterize USPIO uptake across immune and nonimmune cell populations. For extra-axial tumors such as VS, tumors are often completely resected allowing comparison of ferumoxytol imaging datasets with tissue across the entire tumor volume. For intra-axial tumors such as glioma, image-guided tissue sampling of non-enhancing and enhancing regions on delayed phase (>24 hours) post ferumoxytol imaging can be performed using neuronavigation software.

The interval between the final ferumoxytol MRI scan and tissue acquisition will be recorded. Surgery will be scheduled as close as clinically feasible to the final imaging timepoint, determined by clinical urgency, theater availability and standard care pathways. In line with the usual clinical pathway at our institution, for participants with glioma, it is expected, that surgery will be performed within 24 hours of the final MRI scan. For participants with VS, it is expected that surgery will be performed within 4 weeks of the final MRI scan. Acquired imaging from each timepoint (post GBCA and post ferumoxytol) will be fused using neuronavigation software. For participants with glioma, sampling will target regions within the tumor, where safe and appropriate to do so, corresponding to delayed ferumoxytol related changes, contrast enhancement and non-enhancing tumor. For participants with VS, complete or near-complete resection is standard practice at our institution but we will also use neuronavigation to allow for tissue sampling of different regions within the tumor. Sample location will be recorded for later comparison with MRI-derived maps. Imaging–histology registration will be interpreted with recognition of unavoidable spatial uncertainty arising from brain shift, tissue deformation, sampling limitations, fixation and sectioning effects, and differences between *in vivo* MRI resolution and *ex vivo* histological resolution.

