### Sample size and tumor groups

2.7.

The planned number of participants is 39 (12 sporadic VS, 12 NF2-VS patients, 15 glioma patients). This sample size reflects feasibility and the expected recruitment capacity of a single-center pilot study requiring serial advanced MRI over three days, ferumoxytol infusion, and, in surgical participants, tissue acquisition for imaging-histology comparison. Although glioma and VS are biologically distinct, both are characterized by macrophage-rich inflammatory tumor microenvironments that are implicated in tumor growth, progression and treatment response. The inclusion of both intra-axial gliomas and extra-axial VS permits assessment of our hypotheses across two clinically important CNS tumor settings with differing characteristics.

This pilot study will allow the evaluation of recruitment feasibility, scan completion rates, tolerability, missing data rates, USPIO-sensitive MRI metrics, and preliminary effect sizes for imaging-histology associations. Subgroup analyses by tumor type, VS growth status and glioma transformation status will therefore be interpreted as exploratory, to inform future larger-scale studies.

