### Statistical analysis

2.9.

Differences between ROI volumes on post-GBCA T_1_-weighted and delayed (24–48 hour) USPIO-enhanced T_1_-weighted images will be evaluated using overlap measures, the Dice similarity coefficient (DSC) and Jaccard similarity coefficients (JSC), and the Structural Similarity Index Measure (SSIM) [43,44].

To satisfy primary endpoints, the associations between imaging-derived and tissue-derived parameters will be assessed using Pearson’s product-moment correlation coefficient for approximately normally distributed variables, or Spearman’s rank correlation coefficient for non-parametric or non-linear associations. Secondary analyses will assess temporal changes in imaging metrics, spatial overlap between GBCA and delayed ferumoxytol signal, and associations between USPIO-sensitive metrics and DCE-MRI, ASL and DTI-derived parameters. Comparisons between tumor subgroups, including glioma subtype and VS growth status, will be performed using t-tests or ANOVA where assumptions are met, or suitable non-parametric alternatives where appropriate [14]. These subgroup analyses will be exploratory and interpreted as hypothesis-generating.

Temporal changes in voxel-wise and whole tumor ROI imaging metrics (T_2_, T_2_*, R_1_, QSM-derived susceptibility values) within each tumor voxel will be evaluated using a repeated-measures ANOVA with Greenhouse–Geisser correction for non-sphericity and repeated-measures mixed-effect modeling [45]. Mixed-effects modeling will be preferred where repeated-measures datasets are incomplete. To address multiplicity, analyses will be pre-specified by endpoint hierarchy. For ROI-based secondary analyses involving multiple imaging metrics, false discovery rate correction or Holm–Bonferroni correction will be applied as appropriate. Voxel-wise analyses will be treated as exploratory and will use spatially appropriate correction methods, such as cluster-level correction or false discovery rate correction, where feasible. Findings from these exploratory analyses will be interpreted as hypothesis-generating, rather than confirmatory.

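### The transformed versus non-transformed glioma contrast is set between regions that can share a patient, but the only group-comparison test stated has no patient term

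*Protocol article*

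**What the plan says.** **Unit of the question.** In the Protocol article, section 1.2 (Objectives), the fifth secondary endpoint contrasts USPIO signal change and immune cell density between glioma regions that histology classes as transformed and as not transformed. Hypothesis 5 in the same section places these regions inside a tumor: "regions of higher grade transformation within imaged glioma will show changes on delayed USPIO-enhanced acquisitions", with more TAMs expected there than in non-enhancing tumor.

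**Sampling.** For glioma, section 2.4 (Tissue collection) states: "sampling will target regions within the tumor, where safe and appropriate to do so, corresponding to delayed ferumoxytol related changes, contrast enhancement and non-enhancing tumor". Sample positions are recorded. The number of samples per patient is not given.

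**Analysis.** Section 2.7 groups transformation with patient-level factors: "Subgroup analyses by tumor type, VS growth status and glioma transformation status will therefore be interpreted as exploratory". Section 2.9 states: "Comparisons between tumor subgroups, including glioma subtype and VS growth status, will be performed using t-tests or ANOVA where assumptions are met", with non-parametric alternatives otherwise, and adds: "These subgroup analyses will be exploratory and interpreted as hypothesis-generating". The repeated-measures ANOVA and mixed-effects models in 2.9 are introduced for "Temporal changes in voxel-wise and whole tumor ROI imaging metrics".

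**The concern.** The endpoint is regional, while the analysis text speaks of tumor subgroups. A glioma that holds both kinds of region belongs to neither subgroup. Someone following 2.7 and 2.9 has two natural options.

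- **Test at region level as if samples were independent.** This ignores that samples from one patient are correlated. If patients give both kinds, the pairing is unused and the standard error is too large. If patients give several samples of mainly one kind, the standard error is too small.
- **Class each patient as transformed or not and use one value each.** The test is then valid, but it answers a question about patients rather than regions.

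This is the plan's stated comparison of USPIO signal and TAM density by transformation status, in at most 15 patients. The within-tumor contrast is a main source of precision in so small a sample.

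**Working it through.** **The plan's own figure.** "The planned number of participants is 39 (12 sporadic VS, 12 NF2-VS patients, 15 glioma patients"): 12 + 12 + 15 = 39, which adds up. It rests on feasibility, so there is no power figure to reproduce.

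**Inputs.** From the documents: 15 glioma patients. Assumed, because the documents do not give them: two-sided alpha 0.05; within-patient correlation ρ of 0.3, 0.5 or 0.7 (with values near 0 as a check); a difference of 0.8 SD for power; and the sampling patterns below. Total variance is set to 1, with ρ the part shared within a patient.

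**How far the assumed variance is off.** Divide the true variance of the difference in means by the variance that an independent-samples test assumes.

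*Pattern A: each of 15 patients gives one region of each kind.* True variance 2(1 − ρ)/15, assumed 2/15, ratio 1 − ρ = 0.7, 0.5, 0.3. The test is conservative.

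*Pattern B (extreme): 8 patients give three transformed samples each and 7 give three non-transformed samples each.* Ratio 1 + (3 − 1)ρ = 1.6, 2.0, 2.4. The test is anticonservative.

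*Pattern C (mixed): 8 patients give two transformed and one non-transformed sample, and 7 give three non-transformed.* This makes 16 transformed and 8 + 21 = 29 non-transformed samples.
- Assumed variance: 1/16 + 1/29 = 0.0970.
- True variance: (1 + ρ)/16 + (29 + 42ρ)/841 − 2ρ/29.
- At ρ = 0.5: 0.0938 + 0.0595 − 0.0345 = 0.1187, ratio 1.22.
- At ρ = 0.3 and 0.7 the ratios are 1.13 and 1.31. The test is mildly anticonservative.

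**False-positive rate of the independent-samples t-test on regions** (simulation, 40,000 replicates, nominal 0.05):

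| Pattern | ρ = 0.3 | ρ = 0.5 | ρ = 0.7 |
|---|---|---|---|
| A, both kinds, one each | 0.020 | 0.008 | 0.001 |
| B, one kind only, three each | 0.124 | 0.173 | 0.220 |
| C, mixed | 0.066 | 0.080 | 0.095 |

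A normal approximation for B, 2[1 − Φ(1.96/√ratio)], gives 0.121, 0.166 and 0.206, in line with the simulation. At ρ = 0 every pattern is at about 0.05. In A and B, an analysis on patient means (paired in A, unpaired in B) stayed at 0.048 to 0.051.

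**Power in pattern A at 0.8 SD.** The paired test has noncentrality 0.8/√(2(1 − ρ)/15) on 14 degrees of freedom. At ρ = 0.5 this is 0.8 × √15 = 3.10, giving 82%.

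| Test | ρ = 0.05 | ρ = 0.3 | ρ = 0.5 | ρ = 0.7 |
|---|---|---|---|---|
| Unpaired | 56% | 57% | 59% | 60% |
| Paired | 55% | 68% | 82% | 96% |

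**One value per patient.** An 8 versus 7 split at 0.8 SD has noncentrality 0.8/√(1/8 + 1/7) = 1.55 on 13 degrees of freedom, about 30% power. Its error rate is correct, but the comparison is between patients.

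**The case against.** The case against is substantial, and much of it stands.

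- **The test sentence names glioma subtype, not transformed regions.** True. The link runs through 2.7, where transformation status is called a subgroup analysis. But the list in 2.9 is introduced as non-exhaustive, and 2.9 offers no other group-comparison method.
- **Section 2.7 may mean a patient-level analysis.** Possible: section 2.2 admits patients with or without radiological signs of transformation. Such a test would be valid. The regional endpoint would then have no stated group-comparison method of its own.
- **The word unpaired never appears.** True. A reader might infer that the plan discards pairing and that its test has a wrong error rate as a matter of fact. The documents do not support that: t-tests and ANOVA have paired and repeated-measures forms. Independence is only the natural reading of a comparison between tumor subgroups.
- **The size and direction are assumed.** True. They depend on the correlation and the sampling mix, and section 2.4 makes sampling conditional on safety.
- **A reader might infer that the effect sizes meant for planning later studies are compromised.** That goes too far. The preliminary effect sizes in 2.7 are those for imaging-histology associations, not this contrast.
- **A condensed article may leave model detail elsewhere.** This covers a missing detail. It does not cover the mismatch between a regional endpoint with within-tumor sampling and a subgroup framing, both of which the article states.

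**Conclusion.** The point holds as a mismatch between the unit of the endpoint and the unit of the stated analysis. It does not show that a wrong test has been prescribed. Followed on its natural reading, the plan either ignores within-patient dependence or turns the question into one about patients.

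At assumed correlations of 0.3 to 0.7, the first route costs 11 to 36 percentage points of power when each patient gives one region of each kind (68 − 57 and 96 − 60). It raises the false-positive rate to about 7-10% in the mixed pattern and 12-22% in the extreme one. There is no single direction, and near zero correlation no material effect.

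Because the analysis is labelled exploratory, the consequence is a misstated standard error and lost precision, not a false confirmatory claim. The change is worth making because it is nearly free.

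**What to change.** **Section 2.9.** Add a statement to this effect: *Glioma regions classed by histology as transformed or non-transformed will be compared at sample level with a linear mixed model, with transformation status as fixed effect, a random intercept for patient, and a small-sample degrees-of-freedom correction. As a sensitivity analysis, patients with both kinds of region will be compared by a paired t-test or signed-rank test on per-patient region means.* Keep t-tests and ANOVA for comparisons with one value per patient.

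**Section 2.7.** Distinguish region-level transformation status, which can vary within a patient, from any patient-level subgroup by transformation.

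**Cost.** A few sentences of wording; no new patients, samples or scans. With 15 patients the between-patient variance will be estimated imprecisely, which is why the degrees-of-freedom correction and the paired check are included. The exploratory label stays.

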#### The role of TAMs in the growth and progression of CNS tumors

1.1.1.

Low-grade gliomas (LGGs), including diffuse astrocytomas, account for approximately 10–20% of all primary brain tumors. Although they are more indolent relative to grade III (anaplastic) or grade IV tumors including glioblastomas (GBMs), over 95% of LGGs will undergo malignant transformation into a higher grade (III/IV) gliomas (HGGs) [2]. Depending on tumor location, glioma typically present with seizures, focal neurological signs, or symptoms of raised intracranial pressure and these tumors have a disproportionate impact on patients and wider society, often affecting young adults [3]. In other non-CNS cancers, TAMs are known to be pivotal in driving malignant transformation and may contribute to an LGG’s propensity for infiltration, recurrence and therapy resistance [4–7]. Currently, the appearance of focal contrast enhancement within these tumors, suggestive of loco-regional blood–brain barrier (BBB) disruption, is the most used sign of tumor progression in clinical practice. However, this lacks specificity, with the temporal relationship between histological transformation and appearance of new contrast enhancement unclear [8,9].

VS are histologically benign tumors, arising from Schwann cells lining the vestibulocochlear nerve at the cerebellopontine angle [10]. Whilst 95% occur as a unilateral, sporadic tumor, they can also occur bilaterally as part of the syndrome NF2-related Schwannomatosis (NF2-SWN) [11]. The associated morbidity of VS and their treatment (surgery or radiosurgery) makes management through surgery or radiotherapy particularly challenging [12]. *Ex vivo* VS tissue analysis studies have shown that TAMs compartmentalize within Antoni type B areas and are associated with increased tumor size and growth rate [13]. *In vivo* evidence for increased TAM-dependent inflammation with growing VS also stems from TSPO positron emission tomography (PET) studies, where inflammation in growing tumors is attributed to the abundance of TAMs [13]. Subsequent work demonstrated that TAMs are a targetable driver of the immune microenvironment and tumor growth in NF2-SWN-associated VS also [14–16].

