### Objectives

1.2.

In this pilot study, we investigate the candidate USPIO agent ferumoxytol as a noninvasive imaging marker of TAM-driven inflammation in suspected transforming LGGs and VS. We hypothesize that delayed ferumoxytol-sensitive MRI signals reflect the transition from vascular circulation to extravascular and TAM-associated USPIO uptake within the tumor microenvironment.

The primary endpoint is to assess the association between delayed ferumoxytol-induced MRI susceptibility changes and histologically quantified TAM density, across CNS tumor subtypes with differing vascular and microenvironmental characteristics. Within this, the specific secondary endpoints are to:
Characterize the volume, pattern, and intensity of early and delayed USPIO-enhanced MRI signal in gliomas and VS and define the optimal qualitative (e.g., susceptibility-weighted imaging, SWI) and quantitative methods (e.g., quantitative susceptibility mapping, QSM and T2* mapping) for assessing delayed USPIO cellular internalization.Examine the relationship between GBCA enhancement patterns and the extent, spatial distribution and signal intensity of early (<2 hours) and delayed (24–48 hours) USPIO uptake in both glioma and VS cohorts.Examine the association between delayed USPIO-enhanced MRI signal, tissue markers of TAM abundance and VS clinical behavior, such as size and VS growth status.Evaluate QSM-derived susceptibility values as a quantitative imaging marker for detecting USPIO cellular internalization in CNS tumors, and the relationship with tissue measures of iron abundance and localization.Assess differences in USPIO-related signal changes and immune cell density between histologically confirmed transformed and non-transformed glioma regionsEvaluate the phenotype and spatial distribution of TAMs in each tumor and their relationship to USPIO uptake

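### Vestibular schwannoma growth is analysed only as growing versus non-growing; the association with continuous growth rate should be pre-specified beside that comparison, as a cheap exploratory addition

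*Protocol article*

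**What the plan says.** Section 1.2 of the protocol article states hypothesis 4 as a two-group contrast: delayed susceptibility measures (QSM, R2*) "will be greater in growing VS, relative to non-growing tumors, and will reflect an increased abundance of TAM in these tumors". The third secondary endpoint, in the same section, concerns the association of delayed signal with "tissue markers of TAM abundance and VS clinical behavior, such as size and VS growth status".

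Section 2.9 names the test: "Comparisons between tumor subgroups, including glioma subtype and VS growth status, will be performed using t-tests or ANOVA where assumptions are met". If those assumptions fail, it falls back on a non-parametric test, which is also a group comparison. Growth rate as a continuous variable appears in no analysis that the article names.

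The rationale in section 1.1.1 has two strands. Tissue studies are cited to the effect that "TAMs compartmentalize within Antoni type B areas and are associated with increased tumor size and growth rate", which is a graded relation. PET studies are cited "where inflammation in growing tumors is attributed to the abundance of TAMs", which treats growing tumours as a class.

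Section 2.2 recruits both growing and static VS without stating a split. Section 2.7 plans 12 sporadic VS, 12 NF2-VS and 15 glioma participants on grounds of feasibility. Sections 2.7 and 2.9 both call the comparison by growth status exploratory.

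**The concern.** If macrophage burden rises with the speed of growth, the two-group test discards the information that would show it. A slow and a fast grower count as the same, while two tumours on either side of the cut count as opposites. With at most 24 VS participants for imaging, and fewer with tissue, this matters for an analysis meant to generate hypotheses: a gradient could be present and the named analysis could not display it.

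Correlation methods are already in section 2.9 for the imaging-tissue associations, but are not named for growth. A growing or static label has to come from repeated size measurements, so a rate should be obtainable from the same scans. That those scans are available for every participant is an assumption.

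**Working it through.** **Inputs from the article.** VS participants: 12 + 12 = 24 (check: 24 + 15 = 39, the planned total). The article gives no power figure, effect size, significance level or growing/static split, so there is no stated figure to reproduce.

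**Assumptions.** n = 24, imaging only; 12 growing and 12 static; two-sided 5%; correlation rho of 0.4, 0.5 or 0.6 between the imaging metric and true growth rate.

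**Check by formula.** If rate and metric are bivariate normal, a median split multiplies the correlation by sqrt(2/pi) = 0.798. Efficiency falls to about 0.798² = 0.637, so 24 tumours carry the information of about 24 × 0.637 = 15.3. Approximate power is Phi(atanh(r) × sqrt(n − 3) − 1.96). For rho = 0.5:

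- continuous: atanh(0.5) × sqrt(21) = 0.549 × 4.583 = 2.517; 2.517 − 1.96 = 0.557; power 71%
- split: r = 0.5 × 0.798 = 0.399; 0.4225 × 4.583 = 1.936; 1.936 − 1.96 = −0.024; power 49%

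The loss is about 22 points.

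**Simulation** (40,000 replicates per cell). In the half-static scenarios, 12 tumours have true rate 0 and 12 have rate 0.2 + Exp(1). The observed rate adds normal measurement noise with the SD shown, and the growing/static label is taken as error-free. In the step scenario the metric depends only on the label, and rho is its correlation with the label; noise SD is 0.1.

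| Scenario | rho | t-test | Spearman | Pearson |
|---|---|---|---|---|
| Normal rates, median split | 0.4 / 0.5 / 0.6 | 33 / 50 / 69% | 45 / 66 / 85% | 51 / 73 / 90% |
| Half static, noise SD 0.1 | 0.4 / 0.5 / 0.6 | 24 / 35 / 50% | 31 / 45 / 61% | 48 / 67 / 83% |
| Half static, noise SD 0.5 | 0.4 / 0.5 / 0.6 | 24 / 36 / 50% | 25 / 36 / 48% | 39 / 55 / 71% |
| Half static, noise SD 0.8 | 0.4 / 0.5 / 0.6 | 24 / 36 / 51% | 20 / 28 / 38% | 31 / 44 / 57% |
| Pure step | 0.4 / 0.5 / 0.6 | 53 / 77 / 94% | 40 / 61 / 81% | 27 / 41 / 57% |

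**Reading.**

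- Graded relation, well-measured rates (rows 1 and 2): the t-test falls short of Spearman by 7 to 16 points and of Pearson by 18 to 33. Separate runs with 4,000 replicates, where one power estimate has a standard error of up to sqrt(0.25/4000) = 0.8 points, widen this to about 6 to 16 and 17 to 34. The wider ranges are the ones quoted.
- Noisy rates, half static: at noise SD 0.5 Spearman gains nothing and at 0.8 it loses. Pearson keeps an advantage of about 15 to 20 points, then about 7 to 8.
- Pure step: the group test is ahead of Spearman by about 13 to 17 points and of Pearson by about 27 to 37.

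The range also depends on the split and on rho. In the normal scenario, over rho 0.2 to 0.8, the t-test's loss against Pearson is about 3 to 23 points at 1:1 and 4 to 26 at 1:2 or 2:1.

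**The case against.** The planned test matches the plan's own framing. Hypothesis 4 is worded as growing versus non-growing, recruitment is described by that status, the endpoint names growth status, and the PET strand of the rationale concerns growing tumours as a class. The analysis is exploratory in a feasibility-sized pilot with no power target, so no stated error rate or primary conclusion is affected. The endpoint's wording, "VS clinical behavior, such as size and VS growth status", gives examples and does not exclude a continuous measure. The full analysis plan is not shown and may already contain one. All of this stands, and it limits the weight of the point.

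Three stronger readings are tempting, and the documents do not support them.

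- A reader might infer that the group comparison is wrong and should give way to the continuous one. The table shows a trade-off that depends on the shape of the relation and the quality of the rates, neither of which the article states.
- A reader might infer that the plan contradicts its rationale. Growth rate is only one of the two strands in section 1.1.1.
- A reader might infer that the cut distorts the preliminary effect sizes promised in section 2.7. Those concern imaging-histology associations, which section 2.9 already analyses by Pearson or Spearman.

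What survives is narrower: the named analyses include nothing that could show a gradient with growth rate, and adding one costs little.

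**Conclusion.** The point holds as a cheap improvement, not as an error. The article commits hypothesis 4 to a two-group test, whether parametric or not, while part of its rationale is a relation with growth rate. Given a linear relation with correlation 0.4 to 0.6, well-measured rates, 24 tumours split 12:12 and a two-sided 5% level, the group test gives up about 6 to 16 points of power against Spearman and 17 to 34 against Pearson. None of these inputs except the 24 is in the article, and 24 applies to imaging only: the macrophage-density part needs tissue, and some VS participants are under surveillance or considered for bevacizumab. Because the advantage shrinks with noisy rates and reverses under a pure step, the evidence supports running both analyses and does not support ranking the continuous one first.

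**What to change.** In section 2.9, keep the growing versus non-growing comparison and add a sentence that pre-specifies, beside it, the association of delayed susceptibility with continuous pre-study growth rate, and of macrophage density with growth rate where tissue exists. Define growth rate as annualised change in tumour size from the scans already used to assign growth status. Analyse it by correlation or regression with a confidence interval, account for sporadic versus NF2 type, and label it exploratory. If the full analysis plan already has this, a reference to it is enough.

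The cost is one sentence and a tabulation of growth rates from existing scans, assumed available; no new patients, scans or procedures are needed. The downsides are one more exploratory analysis to report, and measurement error and unequal scan intervals in the growth rates.

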### Eligibility criteria

2.2.

Two main tumor groups of participants will be recruited for this study.

Group A: Patients with either sporadic or NF2-SWN-associated VS. The sample will include growing tumors that are being considered for surgical resection (sporadic tumors) or treatment with the anti-angiogenic agent bevacizumab (NF2-SWN-associated VS), and non-growing/static tumors that are being considered for either further radiological surveillance or surgery.

Group B: Patients with a suspected transforming LGG. Patients in this cohort will have a suspected diagnosis of an LGG on conventional clinical imaging, with or without radiological features suggestive of malignant transformation toward either grade III (anaplastic) or grade IV gliomas. Patients who are listed to undergo surgical debulking or biopsy will be enrolled into the study so that acquired imaging can be compared with tissue datasets.

*Inclusion criteria*:
Be at least 16 years oldHave a CNS tumor suspected to be one of the defined histological typesBe able to lie still for up to 1 hour comfortably

*Exclusion criteria*:
Life expectancy of <1 yearPrevious CNS radiotherapy/stereotactic radiosurgery (SRS)Pregnancy/ breastfeeding in femalesAn eGFR of <30 ml/minA documented history of iron overload/hemosiderosis/hemochromatosisPresence of other immune or inflammatory conditions e.g., rheumatoid arthritisAbsolute (e.g., pacemaker) or relative (severe anxiety or claustrophobia) contraindications to MRI scanningA history of allergic reaction to iron or dextranA history of allergic reaction to gadolinium contrast agents, asthma or renal problemsInability to understand verbal explanations or written information given in English.

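### The growing-versus-static VS comparison does not name sporadic versus NF2 status as a factor, so a t-test could carry a difference between those groups into the hypothesis 4 contrast

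*Protocol article*

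**What the plan says.** **Hypothesis.** Section 1.2 (hypothesis 4) predicts that susceptibility-based measures of delayed USPIO uptake "will be greater in growing VS, relative to non-growing tumors, and will reflect an increased abundance of TAM in these tumors". This is a single contrast across VS, with no reference to NF2 status.

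**Recruitment.** Section 2.7 sets the groups: "The planned number of participants is 39 (12 sporadic VS, 12 NF2-VS patients, 15 glioma patients"). Section 2.2 describes how growing tumors arrive: "The sample will include growing tumors that are being considered for surgical resection (sporadic tumors) or treatment with the anti-angiogenic agent bevacizumab", the second route being for NF2-SWN-associated VS. Static tumors enter from surveillance or surgery. No number of growing or static tumors is set, either overall or within a group.

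**Analysis.** Section 2.9 gives the method: "Comparisons between tumor subgroups, including glioma subtype and VS growth status, will be performed using t-tests or ANOVA where assumptions are met". Rank-based or similar tests are the fallback. No adjustment or stratification factor is named. Mixed-effects models appear in 2.9 only for change over time. Sections 2.7 and 2.9 both call the growth-status comparison exploratory.

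**The concern.** Sporadic versus NF2 status is a known design factor. The different routes of entry give no reason to expect the same share of growing tumors in each group, and nothing in the plan makes the shares equal. If the two groups differ in the imaging metric for reasons unrelated to growth, a two-sample t-test attributes part of that difference to growth. Depending on direction, this could produce an apparent growth effect or hide a real one.

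At stake is the estimate for hypothesis 4. No confirmatory decision rests on it, but section 2.7 says the subgroup analyses are to inform larger studies. An effect size carried into their design should not be partly a contrast of NF2 with sporadic disease.

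**Working it through.** **Inputs from the article.** 12 + 12 + 15 = 39 participants, which reproduces the stated total; 24 of them have VS. There is no power figure to reproduce: "This sample size reflects feasibility and the expected recruitment capacity of a single-center pilot study".

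**Assumed inputs.** The article gives none of the following:
- one tumor per patient;
- within-cell SD of 1;
- two-sided 5% level;
- NF2-sporadic difference of 0, 0.5 or 1 SD;
- three growth splits;
- a growth effect of 0 (for bias and type I error) or 1 SD (for power).

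**Step 1: bias of the unadjusted difference.**

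Bias = [P(NF2 | growing) − P(NF2 | static)] × NF2 difference.

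- 9/12 NF2 and 5/12 sporadic growing: 14 growing, 10 static. 9/14 − 3/10 = 0.343.
- 10/12 and 4/12: 14 growing, 10 static. 10/14 − 2/10 = 0.514.
- 6/12 and 6/12: 6/12 − 6/12 = 0.

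**Step 2: type I error**, by simulation of a t-test against a linear model with growth and NF2 terms, no growth effect present:

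| Growing NF2 / sporadic | NF2 difference | Bias, t-test | Type I error, t-test |
|---|---|---|---|
| 9 / 5 | 0 | 0 | 5% |
| 9 / 5 | 0.5 SD | 0.343 × 0.5 = 0.17 | about 6% |
| 9 / 5 | 1 SD | 0.34 | about 9% |
| 10 / 4 | 0 | 0 | 5% |
| 10 / 4 | 0.5 SD | 0.514 × 0.5 = 0.26 | about 8% |
| 10 / 4 | 1 SD | 0.51 | about 17% |

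The model with both terms has no bias and about 5% in every row.

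**Step 3: the opposite direction.** With a 9/5 split, an NF2 difference of −1 SD and a true growth effect of 1 SD, power is about 26% for the t-test and 58% with the NF2 term.

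**Step 4: equal growth mix (6/6).** There is no bias. For a 1 SD growth effect, power is 65% with either analysis if the NF2 difference is 0. It is 63% unadjusted against 65% adjusted at 0.5 SD, and 55% against 65% at 1 SD.

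**Step 5: price of adjustment.** With no NF2 difference, the sampling standard error of the growth effect is:

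- unadjusted: 1/√(n_growing × n_static / 24);
- adjusted: 1/√(sum over the two groups of n_growing × n_static / 12).

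For 9/5: unadjusted 1/√(14 × 10/24) = 0.41; adjusted 1/√(9 × 3/12 + 5 × 7/12) = 0.44.

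For 10/4: unadjusted 0.41; adjusted 1/√(10 × 2/12 + 4 × 8/12) = 0.48.

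Adjustment thus widens the standard error when growth and NF2 status are associated. Set against the bias, root mean squared error still favors adjustment when the NF2 difference is 1 SD: at 9/5, √(0.414² + 0.343²) = 0.54 against 0.44. At 10/4 with 0.5 SD the two are nearly equal: √(0.414² + 0.257²) = 0.49 against 0.48.

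**The case against.** The strongest reply is that the defect is partly read into the text. A reader might infer that the plan pools the two VS groups and ignores NF2 status. It does not say so. Section 2.9 lists families of tests, and an ANOVA can hold NF2 status as a second factor. The article condenses a fuller plan that is not shown, and model terms are often settled there. **This stands against any claim that pooling is planned.** It does not remove the point, because the article offers a t-test for this comparison and a two-sample t-test cannot hold the second factor.

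A reader might also infer that the unadjusted analysis is both biased and less precise than it need be. **That does not hold in general.** The precision gain needs a real NF2 difference and a near-equal growth mix, and an equal mix removes the bias. Under imbalance, adjustment removes bias but can widen the standard error.

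Third, the NF2 difference and the splits are assumptions, and nothing in the article shows that imbalance is likely. **This stands**, so the result is a range that includes zero.

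Fourth, the comparison is labeled exploratory, and the preliminary effect sizes mentioned in section 2.7 are those for imaging-histology associations. **This limits the consequence.** The label restrains claims of significance, but it does not remove bias from an estimate meant to inform later work.

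**Conclusion.** The point holds as a risk of confounding that the stated t-test leaves open. It is not a demonstrated error. It requires both a difference between NF2 and sporadic tumors in the metric and a different growth mix in the two groups; if either is absent there is no bias. Under the two unequal splits examined and NF2 differences of 0.5 to 1 SD, the bias is 0.17 to 0.51 SD and type I error is about 6% to 17%. The article supplies neither the difference nor the splits. Because the analysis is exploratory, the harm is a misleading preliminary estimate for hypothesis 4. A change is advisable because it is cheap and uses information that already defines recruitment.

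**What to change.** In section 2.9, state that VS growth status will be analysed with growth status and sporadic/NF2 status as factors, by two-way ANOVA or a linear model. Where assumptions fail, use a rank test stratified by NF2 status, so that the non-parametric route is kept. Report the four growth-by-NF2 cell counts and show the growth difference within each group descriptively, since the additive model assumes a common growth effect that 24 tumors can hardly test. Keep the exploratory label.

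**Cost:** one sentence, one degree of freedom and no new data. The standard error will be wider if growth and NF2 status prove strongly associated (0.48 against 0.41 SD at the 10/4 split). The cell counts will let readers see when that is so.
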